### 8.2.1 OBJECTIVES OF ANALYSES AND STUDY VARIABLES

To estimate the long term effects (week 26, week 52 and week 104) of an *ad libitum* diet with high or normal protein content and with high or low GI, compared to a control diet.

### 8.2.2 MAIN OUTCOME MEASURES

The main outcome measures in this study for adults are body weight loss maintained (kg), changes in body composition (DEXA/bioimpedance), proportion of subjects maintaining > 0, 5 and 10% of initial weight loss, and drop-out rate. Main outcome measures for children are changes in the proportion of overweight and obese children at 6 and 12 mo, and changes in age-associated BMI, % whole body fat and drop-out rate.

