Primary outcome measures for adults are body weight loss maintained (kg), change in body composition, proportion of subjects maintaining > 0, 5 and 10% weight loss, and drop-out rate. Other non-clinical primary measures are to identify biological and psychological traits that determine the family's and individual's responses to the dietary interventions. Secondary end-points are reduction in abdominal obesity, changes in risk factors of type-2 diabetes and CVD and appetite/satiety hormones, and changes in physical activity. Clinical measurements will include in addition the identification and quantification of adipose tissue mRNA and peptide biomarkers. Primary outcome measures for children are changes in the proportion of overweight and obese children at 6 mo, and changes in BMI, and % whole body fat. Secondary end-points for overweight children are reduction in abdominal obesity, changes in waist-hip circumference ratio and blood parameters and changes in physical activity. A sub-study (described below) will assess the effect and safety of the high protein diet in children and adolescents. Dietary effects on bone and kidney health will be assessed and primary safety end-points will include changes in urinary and blood proteins, such as albumin and creatinine.

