### **Intervention outcome measures**

During the intervention study, questionnaires and 3-day food records will be completed by all adult subjects, and fat biopsies and fasting blood samples will be taken, anthropometric measurements (weight, body composition, etc) and 24h urine collections will be made and oral glucose tolerance tests (OGTT) will be performed. Some adult subjects are involved in specific sub-studies (described in Section 6).

The overweight children (aged 5 - 18) will also complete 3-day dietary records, and will have blood and urine samples taken (but not fat biopsies) for measurement of safety factors and certain hormones, and will also undergo anthropometric measurements (height, weight etc). Normal weight children will undergo anthropometric measurements and have blood and urine samples taken for measurement of safety factors only. All these measures and the visits planned are described in more detail ahead (Section 9).

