### 5.1 INCLUSION CRITERIA

The inclusion criteria for the families are as follows:

- Families where both parents are < 65 years old, and where minimum one adult parent is obese (BMI>30) and the other parent is BMI>28.
- Families with 1-3 children, where at least one child aged between 5 and 18 years is overweight (defined according to Cole *et al.* (2), i.e. with an iso-BMI>25).
- Single-parent families with one obese (BMI>30) parent and minimum 1 overweight child aged between 5 and 18 years. Any other adult family members (including offspring) are excluded from the study. Children above the age of 16 may be excluded if they so wish.
- Healthy and no regular medication (exception oral contraceptives)
- All ethnic groups are allowed inclusion
- Smoking is allowed, provided subjects do not intend to change their smoking behaviour.
- All subjects should have an overall physical and psychological condition that the investigator believes is in accordance with the overall aim of the study.

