### 8.2.5 PRIMARY HYPOTHESIS

The following primary hypothesis can be applied:

H0: The 1o outcome (weight, etc) is equal in the intervention groups at week 26 and week 52, when controlling for the value in CID2 (adults) or CID1 (children).

vs.

H1: The 1o outcome is different in the intervention groups at week 26 and week 52, when controlling for the value in CID2 (adults) or CID1 (children).

The changes in continuously distributed variables from baseline to week 26 and week 52 within treatment groups will be tested with the paired t-test or the Wilcoxon-Signed-rank test, depending on distribution (all tests two-sided).

All categorical variables will be expressed in contingency tables and analyzed using Fisher's exact test. Survival analysis using the Kaplan-Meier plot and the log-rank test will be used to investigate time to subject withdrawal.

All null hypotheses comparing groups assume equality between the treatment groups while the alternative hypotheses assume that there is a difference (two-sided). All within-group null hypotheses assume no change from baseline to week 26 or week 52 while the alternative hypotheses assume that there is a change (two-sided).

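### The children's main outcome, change in the proportion overweight or obese, is not split by baseline weight status, so it nets remission against new onset and loses power

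*Protocol*

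**What the plan says.** - **Outcome.** Section 8.2.2 lists "changes in the proportion of overweight and obese children at 6 and 12 mo" among the children's main outcomes. The synopsis (Aims) has "Primary outcome measures for children are changes in the proportion of overweight and obese children at 6 mo, and changes in BMI". Neither gives a denominator.
- **Contrast with the secondary outcomes.** In the synopsis these are limited by weight status: "Secondary end-points for overweight children are reduction in abdominal obesity". Section 8.2.3 does the same. The main outcome carries no such limit.
- **Who the children are.** Section 5.1 admits "Families with 1-3 children, where at least one child aged between 5 and 18 years is overweight". Siblings may be of normal weight, and the synopsis (Intervention outcome measures) says "Normal weight children will undergo anthropometric measurements". Section 7.1.2 schedules weight and height for all children at every CID.
- **Analysis.** Section 8.2.5 states "All categorical variables will be expressed in contingency tables and analyzed using Fisher's exact test". Section 8.2.4 applies ANACOVA to the main outcome measures with CID 1 as the covariate for children, and the hypothesis in 8.2.5 also controls for the CID 1 value.
- **Allocation.** Section 4.2 randomises about 11 families to each of five groups, stratified by centre, number of obese parents and BMI. Neither the number nor the weight status of the children is a factor.
- **BMI and timing.** The synopsis names plain BMI and gives the proportion at 6 months. Section 8.2.2 names age-associated BMI and gives the proportion at 6 and 12 months.

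**The concern.** The outcome repeats an entry criterion for some of the children in its denominator. A child who is overweight or obese at CID 1 can improve the proportion only by remission. A sibling of normal weight can only worsen it. One net figure answers neither of the questions the protocol asks of children: whether overweight children lose their overweight, and whether weight gain is prevented in the others. The net figure also shrinks as more normal-weight siblings are enrolled, even when the diets work equally well. A test on follow-up status that ignores CID 1 status then carries sibling mix as noise. At stake is the ability to see and interpret a diet effect in children.

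**Working it through.** The protocol gives no rate or sample size for this outcome, so there is no figure to reproduce. Remission, onset and sibling numbers below are assumptions.

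**1. Effect of the sibling mix.** Let w be the share overweight or obese at CID 1, r the remission rate and i the new-onset rate. Then:

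change in pooled proportion = -w·r + (1 - w)·i

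Take 11 overweight children (one per family, section 4.2), r = 20% and i = 5%, the same in every arm.

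| Normal-weight siblings | w | Change, points | Change if i = 0 |
|---|---|---|---|
| 0 | 11/11 = 1.000 | -20.0 | -20.0 |
| 4 | 11/15 = 0.733 | -13.3 | -14.7 |
| 11 | 11/22 = 0.500 | -7.5 | -10.0 |
| 22 | 11/33 = 0.333 | -3.3 | -6.7 |

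Dilution occurs even when no sibling becomes overweight. Full cancellation needs w·r = (1 - w)·i. At r = 20% this means i = 20% with 11 siblings, or i = 10% with 22.

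**2. Chance differences between arms.** Simulation of 100,000 pairs of arms: one overweight index child per family, 0 to 2 further children with equal probability, each of normal weight with probability 0.7. At 11 families per arm this gives on average 11 × 1 × 0.7 = 7.7 normal-weight and 11 + 11 × 0.3 = 14.3 overweight children. Rates are the same in both arms (20%, 5%). The second row takes the 350 families of the synopsis split equally over five arms: 350/5 = 70.

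| Families per arm | SD of difference in expected change | SD of difference in baseline level |
|---|---|---|
| 11 | 2.9 points | 11.6 points |
| 70 | 1.1 points | 4.6 points |

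The protocol names the change, so the first SD column applies to the outcome as written. The level matters only because an unadjusted Fisher test would be run on follow-up status.

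**3. False positives.** Under these identical rates, pooled Fisher on follow-up status rejects in about 2% of simulated pairs at either size, below the nominal 5%.

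**4. Power.** Remission 10% v 35%, onset 5% in both arms, same sibling model, children treated as independent:

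| Families per arm | Pooled Fisher | Fisher, children overweight at CID 1 only | Test stratified by CID 1 status |
|---|---|---|---|
| 11 | about 12% | about 26% | about 31% |
| 70 | about 78% | about 98% | about 98% |

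**5. The two analysis statements.** Section 8.2.4 would adjust this main outcome for CID 1. The categorical-variable sentence in 8.2.5 would not. CID 1 adjustment would remove much of the mix dependence, but it would still report remission and onset as one figure.

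**The case against.** The strongest reply has five parts.

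- **The denominator is never stated, so pooling is inferred.** True. However, the secondary outcomes are expressly limited to overweight children and this one is not. If overweight children alone were meant, the baseline would be 100% by construction and the outcome would simply be remission. The text needs correcting on either reading.
- **Section 8.2.4 already adjusts for CID 1.** It may. Section 8.2.5 says otherwise for all categorical variables, and nothing says which governs.
- **Families are randomised, so sibling mix is balanced in expectation.** This stands. A reader might infer that the outcome biases the comparison, or that arms with equal effects will typically differ by some 12 points. The 12-point figure is the SD of the level at 11 families per arm; for the change the SD is about 3 points. Extreme mixes can mislead: 0 v 22 siblings at equal rates gives 9/11 v 10/33, p = 0.005. But 4 v 15 siblings gives 9/15 v 10/26, p = 0.21, and the overall rejection rate stays below 5%.
- **Complete cancellation is contrived.** This also stands. It needs onset rates for which the protocol gives no basis. Partial netting and dilution are the likelier effects.
- **Splitting shrinks the denominators.** True: with 11 children per arm, Fisher needs a split such as 0/11 v 5/11 to reach p < 0.05. In the case worked above, separating the sets still gains power.

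The BMI wording is a minor matter. Section 8.2.2 already says age-associated BMI and overweight is defined by iso-BMI, so the protocol does not commit to analysing raw BMI.

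**Conclusion.** The point holds as a definition that should be corrected. The pooled proportion merges two opposite transitions, its size depends on sibling mix (-20 v -7.5 points for the same assumed effects), and the protocol gives two incompatible treatments of CID 1 status for it. The cost is interpretability and power: about 12% against 26% to 31% at 11 families per arm, and about 78% against 98% at 70. The documents do not support a claim of systematic bias or of an inflated false-positive rate. The sizes rest on assumed remission, onset and sibling distributions and on independence of children within a family. The direction of the dilution follows from the formula for any mix that includes normal-weight siblings. Section 8.2.7 sizes the trial only for weight change to week 26, so low power at 11 families per arm is acknowledged there; the avoidable part is what pooling adds.

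**What to change.** In section 8.2.2 and the synopsis, replace the pooled proportion with two outcomes, each at weeks 26 and 52:

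- (a) among children overweight or obese at CID 1, the proportion who are no longer so;
- (b) among children of normal weight at CID 1, the proportion who have become overweight or obese.

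Compare arms within each set, or use one test stratified by CID 1 status. State in 8.2.4 and 8.2.5 that this replaces the unadjusted Fisher test for this outcome. Align the synopsis with 8.2.2 on age-associated BMI and on the 6- and 12-month time points.

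The cost is wording only, since weight and height are already recorded for all children at the CIDs. The drawback is a smaller denominator for each outcome, and few events in (b): under the assumptions above, about 7.7 × 0.05 = 0.4 new cases per arm at 11 families. Outcome (b) would therefore be largely descriptive at that size.

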### 8.2.3 SECONDARY OUTCOMES

Secondary outcomes (adults) are reduction in abdominal obesity, changes in risk factors of type-2 diabetes and CVD, appetite/satiety hormones, waist-hip and sagittal measurements and physical activity. Secondary outcomes for overweight children are reduction in abdominal obesity, changes in blood parameters and waist-hip circumference ratio, and changes in physical activity.

Other secondary aims of the study (in collaboration with other RTD lines) are to identify biological, genetic and psychological traits that determine an individual's (or family's) response to the diet interventions. Biological traits (including age, gender, body weight and composition, family size, and genetic make-up) will be evaluated as potential moderators of response. Psychological traits (including satiety, diet satisfaction, food craving, dietary restraint, disinhibition, and perceived hunger and quality of life) will be evaluated as potential moderators and/or mediators of response. Interaction terms between diet and biological/psychological traits will be used to examine potential moderators, and tests of direct and indirect effects will be used to test whether psychological traits mediate the relationship between diet and weight regain (e.g., What proportion of the effect of diet on weight regain can be explained by the diet's effect on satiety?). Mediation models will only be considered if a significant effect of dietary intervention is observed in the primary analysis.

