### **8.2 STATISTICAL PROCEDURES**

All statistical analysis described in this protocol will be performed by the investigator. All analysis and tabulations will be performed using the latest release of the SAS® or SPSS software or similar statistical software. Appropriate descriptive statistics will be presented for each variable; n=number of patients, mean, median, SD and min-max for continuously distributed variables, and rates and percentages for categorical variables. Statistical tests will be performed using 5% as the nominal level of significance and interval estimates will be constructed using 95% as the level of confidence. Statistical and analytical methods, and sample size considerations are discussed in the following sections. The investigator will make the decisions regarding subjects, or individual values belonging to a patient, to be excluded from the analysis. Subjects will only be excluded from the efficacy analysis when the uses of these are considered a protocol violation, putting the scientific aspects of the trial at risk. The variables that will be statistically tested are given in the Sections concerning primary and secondary variables.

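### Identifying traits that govern response to the diets is a primary measure in the synopsis and a secondary aim in 8.2.3, and its 12–13 interaction tests fall under an unadjusted 5% level

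*Protocol*

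**What the plan says.** Two sections of the protocol give the trait aim a different status.

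- Synopsis, Aims: "Other non-clinical primary measures are to identify biological and psychological traits that determine the family's and individual's responses to the dietary interventions".
- Section 8.2.3: "Other secondary aims of the study (in collaboration with other RTD lines) are to identify biological, genetic and psychological traits", again as determinants of how a person or family responds.

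The method is in 8.2.3: "Interaction terms between diet and biological/psychological traits will be used to examine potential moderators". On the biological side, "Biological traits (including age, gender, body weight and composition, family size, and genetic make-up) will be evaluated as potential moderators of response". Seven psychological traits follow, as moderators and/or mediators: satiety, satisfaction with the diet, craving, restraint, disinhibition, hunger and quality of life. Both lists are introduced as examples, so neither is closed.

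The error level is in 8.2: "Statistical tests will be performed using 5% as the nominal level of significance". The same section gives the scope: "The variables that will be statistically tested are given in the Sections concerning primary and secondary variables". That takes in 8.2.3. The protocol states no multiplicity adjustment, order of testing or exploratory label for the interaction tests.

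**The concern.** The two sections describe the same aim in nearly the same terms, so they cannot be read as two different objectives. The synopsis gives a trait finding primary standing and 8.2.3 does not. Anyone writing the analysis plan or the report would have to choose between them.

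The choice matters because the aim is worded strongly (to identify traits that determine response), while the only error rule that reaches the tests is 5% for each. A dozen or more interaction tests at that level can easily produce one nominally significant trait when none matters. Section 8.2.7 sizes the study only for weight change to week 26 and accepts that other outcomes may be too small to support a conclusion. A lone significant interaction would therefore come from a family of tests that the study was not sized for. What is at stake is the standing of any claim that a particular kind of person does better on a particular diet. The main comparison of weight between diets is not affected.

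**Working it through.** The protocol gives no error rate for the moderator tests, so there is no stated figure to reproduce. The check is what its own rules imply.

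**Inputs**

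- Level per test: 0.05 (8.2). Group comparisons are two-sided (8.2.5).
- Biological traits: 5 if body weight and composition are one item, 6 if they are two. Genetic make-up is counted once.
- Psychological traits: 7.
- Number of tests k, at one per named trait: 5 + 7 = 12, or 6 + 7 = 13.
- One outcome, at week 26. Section 8.2.6 gives week 26 as the time for comparing secondary variables.
- No trait truly moderates the effect of diet.
- Correlation between tests: not in the protocol. Values of 0, 0.3, 0.5 and 0.8 are assumed.

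**Independent tests**

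Chance of at least one false moderator = 1 − (1 − 0.05)^k

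- k = 12: 1 − 0.95^12 = 1 − 0.540 = 46.0%
- k = 13: 1 − 0.95^13 = 1 − 0.513 = 48.7%

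Expected number of false moderators: 12 × 0.05 = 0.60 and 13 × 0.05 = 0.65.

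**Correlated tests**

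For k normal test statistics with common correlation ρ and cut-off c = 1.96, the chance is

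1 − ∫ φ(u) [Φ((c − √ρ·u)/√(1−ρ)) − Φ((−c − √ρ·u)/√(1−ρ))]^k du

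| ρ (assumed) | k = 12 | k = 13 |
|---|---|---|
| 0.3 | 39.7% | 41.8% |
| 0.5 | 31.9% | 33.4% |
| 0.8 | 18.6% | 19.2% |

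As a second check, the diet-by-trait F test was simulated with five equal groups, 110 or 500 subjects in total, no true interaction and 1,000 trials per setting. With traits correlated 0.3 it gave 40–44%, and with traits correlated 0.5 it gave 33–37%. Across both methods the correlated range is about 19–44%.

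**Open lists**

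The protocol gives no number of genetic variables. If it were large, independent testing at 5% would give 1 − 0.95^50 = 92.3% for 50 tests in all and 1 − 0.95^100 = 99.4% for 100. Both counts are assumptions, shown only to indicate the direction.

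**Effect of an adjustment**

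A Bonferroni level over the named traits would be 0.05/12 = 0.0042 or 0.05/13 = 0.0038, which keeps the family at 5% or less.

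**The case against.** The strongest case on the other side is that multiplicity rules for secondary analyses usually sit in the statistical analysis plan, which is not shown. The wording in 8.2.3 is also tentative, since it speaks of potential moderators. Section 8.2.2 leaves the trait aim out of the main outcome measures, and 8.2.7 names weight change to week 26 as the primary efficacy parameter. On this view all that remains is one misplaced word in the synopsis.

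Part of this stands. An adjustment may exist elsewhere, and nothing in the protocol says that a single p<0.05 would be reported as an established determinant. But an analysis plan could not settle which of two protocol statements governs, and an adjustment there would depart from the general 5% rule in 8.2. The count of 12–13 is also not firm. Some psychological traits may be examined only as mediators, which would lower it, and the open lists could raise it.

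A reader might infer four stronger points that the protocol does not support.

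- *A false moderator is likely.* On the named traits, one outcome and one week, every figure is below one half.
- *The moderator tests should wait for a significant diet effect.* Section 8.2.3 says "Mediation models will only be considered if a significant effect of dietary intervention is observed in the primary analysis" and sets no such condition for interactions. That is coherent. Mediation presupposes an effect to be mediated, whereas a trait can moderate response with no overall difference between diets. A gate would also not control error across traits once it opened.
- *Weeks 26 and 52 double the count.* This would give 71–74% for 24–26 independent tests. But 8.2.6 analyses secondary variables at week 26 only, so the doubling relies on the disputed primary label.
- *Five arms multiply the tests.* A global diet-by-trait interaction on 4 degrees of freedom is one test at 5%. The protocol does not call for separate contrasts.

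**Conclusion.** The point holds in two parts. First, the protocol contradicts itself on whether finding response traits is primary or secondary. This needs no calculation. Second, under its stated 5% rule the named interaction tests carry about a 46–49% chance of at least one false moderator if independent, and about 19–44% under the assumed correlations. Even the lowest figure is nearly four times the nominal 5%.

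These sizes assume no true moderator, one test per named trait, one outcome at week 26, genetic make-up counted once, and no adjustment set elsewhere. More genetic variables or more outcomes would raise them, and fewer psychological traits tested as moderators would lower them. The finding limits what may be concluded about traits.

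**What to change.** 1. In the synopsis (Aims), remove the word primary from the trait aim so that it matches 8.2.3.
2. In 8.2.3, label the diet-by-trait moderator analyses exploratory.
3. In 8.2.3, require that every interaction tested is reported with its estimate, 95% confidence interval and a p-value adjusted across the listed traits, with genetic markers handled as their own set.
4. State there that no trait will be claimed to determine response on the strength of an unadjusted p<0.05.

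The mediation models can stay as they are, and the moderator work need not be confined to a single outcome. The cost is a few sentences and a routine adjustment, with no change to visits, samples or recruitment. The drawback is that fewer trait findings will reach significance, and those that do will be presented as leads to confirm.
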